**Methods:**

Three hundred and ten households, each including an index case with a recent COVID-19 diagnosis and at least one asymptomatic treatment-eligible household contact, will be randomized to receive 3 doses of 125 μg IFN ß-1a by subcutaneous administration (days 1, 6, and 11), or standard of care. All participants will be followed until day 29.

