## Background

Since the emergence of coronavirus disease 19 (COVID-19) in China in December 2019, there have been over 190 million cases worldwide and more than 4 million deaths to date [1]. Following the Severe Acute Respiratory Syndrome (SARS) in 2002 [2] and Middle East Respiratory Syndrome (MERS) in 2012 [3], SARS-CoV-2 has emerged as the most serious human coronavirus infection in 20 years. In approximately 80% of cases, SARS-CoV-2 infection results in mild to moderate COVID-19, with symptoms similar to common respiratory diseases such as influenza-like illnesses [3]. In 14% of cases, SARS-CoV-2 infection results in severe disease requiring oxygen supplementation and/or mechanical ventilation, with a further 2–75% progressing to respiratory failure, septic shock and/or organ failure [4, 5].

Even with the recent availability of vaccines, global herd-immunity remains elusive. Worldwide efforts to reduce SARS-CoV-2 infection rates continue, with preventative measures including distancing, use of facemasks in public places, and hand hygiene measures. Many countries have also implemented mandatory quarantine and contact tracing [6]. Individuals infected with SARS-CoV-2 shed virus and may be contagious for up to 5 days prior to developing symptoms (‘pre-symptomatic transmission’) [7–9]. Notably, nearly 60% of all infected subjects can shed virus pre-symptomatically [10]. Pre- or even asymptomatic shedding occurs across all age groups, even in children [11], and has contributed to the rapid expansion of the pandemic [7, 10]. Since pre-symptomatic shedding of virus can start up to 5 days prior to symptom onset, any post-exposure prophylaxis intervention for contacts recently exposed to a case could interrupt the spread of the virus.

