### Primary and secondary objectives

The two co-primary objectives of this study are:To determine whether IFN ß-1a treatment reduces the proportion of infected cases shedding SARS-CoV-2 at day 11 after randomization.To determine whether IFN ß-1a treatment reduces the incidence of SARS-CoV-2 transmission from index cases to treatment-eligible household contacts, as measured by any positive upper airway infection evidenced by real-time Polymerase Chain Reaction (RT-PCR), in contacts at day 11 after randomization.

Secondary objectives of this study are:To determine whether in index cases infected with SARS-CoV-2, IFN ß-1a treatment compared with standard of care reduces the duration of SARS-CoV-2 upper airway virus shedding over 28 days following randomization.To determine whether IFN ß-1a treatment affects the incidence of SARS-CoV-2 upper airway infection or serological conversion by study day 29 in household contacts.To determine whether IFN ß-1a treatment compared with standard of care reduces the proportion of infected cases that require hospital admission or die due to COVID-19.To determine the safety of IFN ß-1a in the treatment and prevention of SARS-CoV-2 infection.

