**Fig. 2 Fig2:**
[figure not shown]
Household and participant eligibility

**Table 1 Tab1:** Participant inclusion and exclusion criteria

	Inclusion criteria	Exclusion criteria*
Index cases	• Provided a signed and dated informed consent form • Aged 18 to < 80 years of age • Confirmed SARS-CoV-2 diagnosis by PCR within 72 h of first treatment dose • The first known diagnosis in the household • Not currently enrolled in a clinical trial and agree to not take any other investigational treatments over the next 28 days • Must plan to remain resident in the household during the study • Lives in household with at least one other ‘treatment-eligible household contact	• Inability to take medications orally or by injection • Known sensitivity/allergy to interferons or use of interferons for another indication • Known adverse drug-drug interactions with any study drugs • Malignancy • Known clinical immune deficiency • Pregnancy or unwillingness of female participant of childbearing age to use recognized methods of birth control/contraception during the trial period • Retinopathy • Known grade 4 or 5 chronic kidney or liver disease • Known arrhythmias • Known autoimmune disease or chronic inflammatory disease • Chronic liver disease • Hospitalization for depression in the last 3 months • Current suicidal ideation • Previous therapeutic use of IFN
Treatment eligible contact	• Provided a signed and dated informed consent form • Aged 18 to < 80 years of age • Not currently enrolled in a clinical trial and agree to not take any other investigational treatments over the next 28 days • Must plan to remain resident in the household during the study • No history of previously confirmed SARS-CoV-2 diagnosis	
Treatment ineligible contact	• Provided a signed and dated informed consent form, parental informed consent, and assent if applicable • Under 18 years OR ≥ 80 years of age OR aged 18 to < 80 years with any contraindication for IFN treatment listed in ‘exclusion criteria’ • Not currently enrolled in a clinical trial and agree to not take any other investigational treatments over the next 28 days • Must plan to remain resident in the household during the study • No history of previously confirmed SARS-CoV-2 diagnosis	

^*^All household members are ineligible if participation by any member is declined or if the index case has been in complete self-quarantine from other household members during the 48 h prior to diagnosis of SARS-CoV-2 infection

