### Baseline and follow-up home visits

Refer to Table 2. To maintain isolation of index cases and their household contacts, all biological samples for the study will be collected during home visits. Home visits will be conducted by appropriately trained trial staff. Staff teams will be composed of a physician and a nurse. All will be trained in Good Clinical Practice and study procedures.

**Table 2 Tab2:** Protocol for home-visit procedures and data collection

	Procedures
Day 1	Medical history Brief physical examination Vital signs (forehead temperature, pulse, blood pressure, pulse oximetry) Document weight and height Review baseline symptoms, if applicable Document concomitant medications and therapies Baseline adverse event assessment Saliva sample collection Nasal brushing for transcriptomics Nasal lining fluid sampling for IgA Blood sample collection (2 tbsp; about 30 ml) Dispense and instruct on use of diary cards Dispense individual thermometers for each participant Urine sample collection and pregnancy test pack, if applicable Administer acetaminophen 1000 mg PO pre-medication, if applicable Study drug administration, if applicable Observation for 20 min post study drug administration, if applicable General education to patients and family members about COVID-19 standard care
Day 6	Brief physical examination Vital signs (forehead temperature, pulse, blood pressure, pulse oximetry) prior to study drug administration Review adverse events Review concomitant medications Saliva sample collection (immediately prior to study drug administration) Nasal lining fluid sampling for IgA Blood sample collection (2 tbsp; about 30 mL) Urine sample collection and pregnancy test pack, if applicable Administer acetaminophen 1000 mg PO pre-medication, if applicable Study drug administration, if applicable Collect completed diary cards and dispense new diary cards Observation for 20 min post study drug administration, if applicable

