### Data analyses

Analyses of data for primary and secondary objectives will be conducted per protocol and through intent-to-treat using the procedures detailed below and described in greater detail in a statistical analysis plan, available upon request. Data analysts will be blind to treatment allocation. Analyses will be conducted using R and statistical coding will be available to the public upon request and approval by the investigators.

#### Analysis for primary objective 1

The Primary Objective 1 is to determine whether IFNß-1a treatment reduces the number of COVID-19 cases still shedding SARS-COV-2 in saliva at day 11 following randomization. Statistical analysis of SARS-CoV-2 RT-PCR results from the index case population will be undertaken comparing IFN ß-1a treated index cases to index cases receiving only standard of care. A linear regression model (binomial family, logit link for dichotomous outcomes) will be applied to data collected, where a risk ratio (and 95% confidence interval) will be reported for the treatment arm variable, adjusted for age, sex, baseline viral load and vaccination status at enrollment.

#### Analysis for primary objective 2

The Primary Objective 2 is to determine whether IFN ß-1a treatment reduces the incidence of SARS-CoV-2 transmission from an index case to treatment-eligible household contacts, as measured by upper airway RT-PCR in contacts at day 11 after randomization. Statistical analysis of SARS-CoV-2 RT-PCR results from household contacts will be undertaken comparing households assigned to IFN ß-1a treatment or standard of care. A linear regression model (binomial family, logit link for dichotomous outcomes) with clustering within a household will be applied, where a risk ratio (and 95% confidence interval) will be reported for the treatment arm variable, adjusted for age, sex, baseline viral load of the index case, vaccination status of the index case, vaccination status of eligible contacts, contacts between index case and household contacts during the initial 11-day period, baseline RT-PCR and antibody levels of treatment eligible contacts at enrollment, number of household members and physical details of the household size, e.g. number of bathrooms, number of bedrooms.

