#### Secondary analyses

Additional analysis of both primary objectives will be conducted to include more rigorous group comparisons, e.g. Fisher’s exact test of proportions and a stratified Cochran-Mantel–Haenszel test of proportions. If the primary analysis method, the generalized linear model with binomial family and log link, does not fit the data well, or converge, a logit link will be used, meaning an adjusted odds ratio and 95% confidence interval will be reported. Specifically, a regression model will be used where the outcome variable is Yes/No for SARS-CoV-2 from the day 11 saliva specimen, with odds ratio and 95% confidence interval reported treatment (active/control) variable, following covariate adjustments. Primary objective 2 analysis will include clustering within households, where appropriate. Secondary outcomes will be reported and analyzed as above for the primary outcomes. Poisson and/or ordinal regression analysis will be conducted to compare days of viral shedding between the IFN treated and standard of care groups. The Cox proportional hazards regression model, with similar adjustments for variables as above, will be employed to examine time based, and specifically time-censored, outcome variables between groups. In addition, Bayesian analyses will be estimated using data-generated distributions of viral shedding at days 11, 16, and 29, and household infection rates. These prior distributions will be used to generate posterior probabilities for the intervention arm.

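### Co-primary 2 pools clearance in contacts already PCR-positive on day 1 with new infection in the rest, so faster clearance alone can be reported as prevented transmission

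*Protocol article*

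**What the plan says.** All references are to the protocol article.

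- **Endpoint.** Under Data analyses, primary objective 2 is the incidence of transmission to treatment-eligible contacts, "as measured by upper airway RT-PCR in contacts at day 11 after randomization". The objectives section words it as "as measured by any positive upper airway infection evidenced by real-time Polymerase Chain Reaction (RT-PCR), in contacts at day 11 after randomization". Under Secondary analyses, the fallback logit model is specified so that "the outcome variable is Yes/No for SARS-CoV-2 from the day 11 saliva specimen".
- **Who is a contact.** For treatment-eligible contacts, Table 1 has one infection-related criterion: "No history of previously confirmed SARS-CoV-2 diagnosis". The Abstract describes a household as including "at least one asymptomatic treatment-eligible household contact". No negative day-1 PCR is asked for.
- **Exposure before day 1.** The Table 1 footnote makes a household ineligible if the index case was fully isolated from the others in the 48 h before diagnosis. The Background says that "nearly 60% of all infected subjects can shed virus pre-symptomatically".
- **Analysis.** The covariates include "baseline RT-PCR and antibody levels of treatment eligible contacts at enrollment". The missing-data section includes every participant, to comply with intention to treat.
- **Specimens.** Saliva is taken on day 1, and on days 6 and 11 with the instruction "Saliva sample collection (immediately prior to study drug administration". Baseline procedures are completed before the household is randomised (Treatment assignment and randomization).

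**The concern.** Contacts have been living with an unisolated index case, so some will be PCR-positive on day 1. Listing their baseline PCR as a covariate shows that the authors expect this. Transmission to these contacts happened before randomisation and cannot be prevented. Their day-11 result shows whether they have cleared the virus, which is the construct of co-primary 1, and the trial is powered on interferon improving it.

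A main-effect covariate gives the two groups different baseline risks but a single arm effect. If interferon speeds clearance and prevents nothing, that coefficient still moves towards benefit. At stake is the Discussion's intended conclusion that treating contacts protects them from infection.

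A second, smaller issue is the specimen. If only the day-11 sample counts, a contact who became positive on day 6 and cleared by day 11 is scored as not infected, and the drug is expected to make that more likely.

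**Working it through.** **1. The plan's own figures.** Co-primary 1: 139 index cases per arm, 85% v 65%, two-sided alpha 0.025, Fisher's exact test gives 93.9% power, consistent with the stated >90%.

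Co-primary 2: 834 contacts (417 per arm), OR 0.5, ICC 0.15. With 834/278 = 3 contacts per household, the design effect is 1 + (3 − 1) × 0.15 = 1.30 and the effective size is 417/1.30 = 321 per arm. No control risk is stated, so there is no single value to reproduce. Power is 80.8%, 88.2%, 92.6% and 96.7% at control risks of 0.20, 0.25, 0.30 and 0.40. The stated >90% therefore needs a control risk somewhere above 0.25.

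**2. Size of the mixture with no preventive effect.** Let q be the share of contacts positive on day 1 and r the risk of new infection, equal in both arms. Neither is given, so both are assumed. Day-11 shedding in baseline-positive contacts is taken as 85% v 65%, the plan's figures for index cases. Then

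- control: 0.85q + (1 − q)r
- interferon: 0.65q + (1 − q)r

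| q | r | Control | Interferon | RR |
|---|---|---|---|---|
| 10% | 10% | 0.085 + 0.090 = 0.175 | 0.065 + 0.090 = 0.155 | 0.89 |
| 20% | 10% | 0.170 + 0.080 = 0.250 | 0.130 + 0.080 = 0.210 | 0.84 |
| 30% | 10% | 0.255 + 0.070 = 0.325 | 0.195 + 0.070 = 0.265 | 0.82 |
| 10% | 30% | 0.085 + 0.270 = 0.355 | 0.065 + 0.270 = 0.335 | 0.94 |
| 20% | 30% | 0.170 + 0.240 = 0.410 | 0.130 + 0.240 = 0.370 | 0.90 |
| 30% | 30% | 0.255 + 0.210 = 0.465 | 0.195 + 0.210 = 0.405 | 0.87 |

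**3. Does adjusting for baseline PCR remove it?** Simulation: 278 households × 3 contacts, ICC 0.15, no effect on acquisition, model with arm and baseline PCR, household-clustered standard errors, two-sided alpha 0.025 (so 1.25% nominal in the direction of benefit), r = 10–30%.

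| q | Adjusted RR | Adjusted OR | False benefit |
|---|---|---|---|
| 10% | 0.89–0.95 | 0.83–0.92 | 4–7% |
| 20% | 0.84–0.91 | 0.69–0.84 | 12–26% |
| 30% | 0.81–0.87 | 0.59–0.74 | 34–57% |

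The higher error rates go with the lower incident risk. At q = 5% the false-benefit rate is 2–4%. With a weaker contrast of 85% v 75% and r = 20%, it is about 4%, 6% and 10% at q = 10%, 20% and 30%. Both scales are shown because the plan reports a risk ratio and falls back to an odds ratio.

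**4. Restricting to day-1-negative contacts.** The same simulated trials give an OR of 0.99–1.03 and false benefit in 0.9–2.1%, close to nominal.

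**5. Day-11-only reading among new infections.** If cumulative infection is equal and shares c0 (control) and c1 (interferon) have cleared by day 11, RR = (1 − c1)/(1 − c0). For an assumed 5% v 15%: 0.85/0.95 = 0.89. For 15% v 35%: 0.65/0.85 = 0.76. The second is an upper illustration, because later infections have less time to clear.

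**6. Power after restriction.** Use 417(1 − q) contacts per arm and design effect 1 + (3(1 − q) − 1) × 0.15. For q = 10%, 20% and 30% this is 375/1.255, 334/1.21 and 292/1.165 effective contacts per arm. At OR 0.5 and control risk 0.30, power falls from 92.6% to 90.6%, 88.0% and 84.5%.

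**The case against.** **The endpoint may be cumulative.** The objectives section speaks of any positive result, which can be read as any positive up to day 11, and the day-11 saliva sentence describes a fallback model. This stands in part. A reader might infer that the plan definitely ignores day-6 positives. The documents do not settle that: the Data analyses wording points to day 11 alone and the objectives wording is open. It is an ambiguity to reconcile, and the pooling problem does not depend on it.

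**A secondary endpoint catches early clearers.** PCR infection or seroconversion by day 29 in contacts is a secondary objective. A reader might infer that the post-exposure question goes unanswered. That is too strong, since this endpoint would help expose a misleading primary result. It cannot, however, correct a co-primary claim.

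**The size rests on assumptions.** This stands. The documents give neither the day-1-positive share nor the incident risk, and 85% v 65% is for index cases, who may be at a different stage of infection. A false-benefit rate above 50% is an unfavourable corner, so ranges are needed. An OR of 0.59 also looks more dramatic than the corresponding RR of about 0.81, which is the scale the plan reports.

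**Dilution of a real effect.** A reader might also infer that prevalent infections would mask true prevention. That is not shown: 85% v 65% is an OR of (0.65/0.35)/(0.85/0.15) = 0.33, stronger than the design OR of 0.5, so on that scale pooling would not dilute it.

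**Contacts may have to be asymptomatic.** The Abstract says so. Table 1 does not, but the eligibility figure is not shown, so its absence from the criteria cannot be asserted. It would not help in any case, because the Background itself says infected people can shed before symptoms.

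**Conclusion.** Wrong as written. The stated aim is incidence of transmission, but the planned analysis includes contacts in whom transmission had already occurred and summarises both groups with one arm effect. Adjusting for baseline PCR does not separate them. Under no preventive effect and the plan's own clearance contrast, the false-benefit rate rises from 1.25% to about 4–7%, 12–26% and 34–57% at 10%, 20% and 30% baseline-positive. It is minor if only about 5% of contacts are positive on day 1, and smaller if interferon changes clearance less than planned. That the analysis mixes two effects follows from the text; how much it matters depends on assumed values. Whether a cleared day-6 positive counts is a separate point of unclear wording.

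**What to change.** 1. Define the co-primary 2 population as treatment-eligible contacts with a negative saliva PCR on day 1, taken before randomisation. Selecting on a pre-randomisation result preserves the randomised comparison.
2. Define the event as any positive scheduled study PCR at day 6 or day 11, and use this definition in the objectives, Data analyses and Secondary analyses sections.
3. Analyse baseline-positive contacts separately, for clearance.
4. Keep day-11 positivity in all contacts as a sensitivity analysis.
5. Add a sensitivity analysis for infections incubating but PCR-negative on day 1, for example excluding day-6 positives. The restriction does not remove these.
6. Restate the power with an explicit control risk and expected day-1-positive share.

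**Cost.** No extra visits or specimens are needed, but the denominator shrinks. At control risk 0.30, power falls below the stated 90% if 20% or more of contacts are positive on day 1 (88.0% at 20%, 84.5% at 30%). The change would also come late: 251 of 310 households were enrolled at submission, the trial is open-label, and its DSMB receives primary-outcome data. It should be a dated amendment, decided and documented by people who have not seen outcome data by arm.

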### Recruitment

Participants will be identified from the list of RT-PCR positive SARS-CoV-2 cases obtained daily from the UC Christus Health Network virology laboratory, COVID-19 outpatient clinics, or the Emergency Rooms. This is a large private, academic health network in Santiago, Chile. Additional patients will be recruited from City Health Departments, local primary care clinics, and through advertising in the community. The recruitment period will continue until the enrollment target is reached.

Cases will be contacted by telephone to explain the study, invite participation, and confirm eligibility. A member of the research team will contact the index case via telephone for a pre-screening discussion (clinical inclusion and exclusion criteria, medical history details and verbal consent). If the participant is eligible to participate, he/she will be provided with a link to an electronic survey, to confirm eligibility and to provide consent to participate. Once an index case has indicated willingness to participate in the study, household contacts will be assessed for eligibility. If at least one household member is considered eligible, he/she will be sent a link to an electronic survey to confirm the reported information. During the recruitment telephone calls, treatment ineligible contacts in each household will be identified and invited to participate in the study.

This pre-consent online approach will reduce face-to-face contact time and the possible exposure of study staff and participants to infection by ensuring all participants are consented and eligibility confirmed, prior to Study Day 1.

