### Treatment assignment and randomization

Households will be randomized as clusters to receive either IFN ß-1a treatment or standard of care, once a household meets all the inclusion and none of the exclusion criteria. Households will be randomized to IFN ß-1a treatment or standard of care at a 1:1 ratio. The minimization technique (biased coin, *p* = 0.7) will be applied to achieve balance between groups stratified by the total number of people within the household. This will be implemented through a platform provided by the Telethon Kids Institute (https://qminim.telethonkids.org.au/).

Households will be randomized during the first home visit, once eligibility is confirmed, participants have signed informed consent, and baseline data collection procedures are completed. Field team members will contact the research laboratory, at which time the household assignment to treatment or standard of care will be made by the randomization software. Participants and study staff will not be blinded to randomization of treatment or standard of care, but all data analyses will be blinded to allocation.

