### Trial status

Participant recruitment started on December of 2020. At the time of manuscript submission, 251 households have been enrolled.

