## Discussion

ConCorD-19 will identify whether early treatment with IFN ß1a offers a therapeutic advantage of accelerated resolution of COVID-19 and whether IFN ß1a treatment of post-exposure contacts protects from infection, thereby reducing transmission. The results from this trial may provide evidence and guidelines for a new outpatient treatment for COVID-19 with mild or moderate disease severity. Treatment interventions are needed, especially with the emergence of variants of concern that are highly transmissible, that may reduce the effectiveness of vaccinations [23].

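### The co-primary 2 (transmission) model leaves out when each household was randomised; this causes no bias but costs up to a few points of power if transmission drifted

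*Protocol article*

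**What the plan says.** All references are to the Protocol article.

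- **Data analyses, primary objective 2.** The transmission model is "adjusted for age, sex, baseline viral load of the index case, vaccination status of the index case, vaccination status of eligible contacts". The list goes on to index-contact exposure, "baseline RT-PCR and antibody levels of treatment eligible contacts at enrollment", household size, and the numbers of bathrooms and bedrooms. Date or period of randomisation is not in it.
- **Data analyses, primary objective 1.** The shedding model is "adjusted for age, sex, baseline viral load and vaccination status at enrollment". It has no calendar term either.
- **Link function.** Both primary-objective paragraphs name a logit link with a risk ratio. The Secondary analyses paragraph calls the log link primary and keeps the logit link and odds ratio as the fallback if the model fits poorly or does not converge.
- **Treatment assignment and randomization.** Households are allocated 1:1 by minimisation with a biased coin of 0.7, "to achieve balance between groups stratified by the total number of people within the household". No other balancing factor is named.
- **Recruitment and Trial status.** "Participant recruitment started on December of 2020". "At the time of manuscript submission, 251 households have been enrolled", out of 310, and "The recruitment period will continue until the enrollment target is reached".
- **Discussion.** The authors point to the "emergence of variants of concern that are highly transmissible".
- **Sample size.** Power above 90% is claimed for co-primary 2: 834 contacts (417 per arm), odds ratio 0.5, two-tailed alpha 0.025, intra-class correlation (ICC) 0.15. No control attack rate is given.

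**The concern.** Calendar period is a household-level factor: households randomised in the same weeks share the circulating variant and the background level of transmission. If these changed during recruitment, they add to the variation between households. Concurrent allocation keeps the arms roughly balanced over time, so this variation contributes little to the difference between arms. A household-robust standard error from a model without period still counts it as random noise. The test is then somewhat conservative and gives up power.

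The covariate list is detailed enough to include rooms in the home, so the absence of randomisation date is a choice fixed in the article rather than a detail left out for brevity. The number of households is fixed and withdrawals are not replaced, so power given up in the model cannot be bought back.

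**Working it through.** **1. The plan's own figure.** With three contacts per household the design effect is 1 + (3 - 1) x 0.15 = 1.30, so the effective number per arm is 417 / 1.30 = 320.8. I used the normal approximation for two proportions (pooled variance under the null, unpooled under the alternative), two-sided alpha 0.025 and odds ratio 0.5:

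| Control attack rate | Power |
|---|---|
| 20% | 80.8% |
| 25% | 88.2% |
| 27% | 90.2% |
| 27.5% | 90.7% |
| 30% | 92.6% |

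The stated figure of more than 90% needs a control rate of about 27% or more. The drift settings below are centred on 27.5%, where it just holds.

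**2. How much variance period could carry.** Assumptions (none is in the article): four equal recruitment periods, evenly spaced control rates with mean 27.5%, and residual ICC 0.12 within period. The share of binary variance due to period is R2 = Var(period rates) / (0.275 x 0.725 = 0.1994). Total ICC = R2 + 0.12 x (1 - R2). The unadjusted variance factor is 1 + 2 x total ICC. With arms exactly balanced over time, the true factor is that minus 3 x R2.

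| Range | Var | R2 | Total ICC | Unadjusted factor | Balanced factor | SE ratio |
|---|---|---|---|---|---|---|
| 20-35% | 0.0031 | 0.016 | 0.134 | 1.268 | 1.221 | 1.02 |
| 15-40% | 0.0087 | 0.044 | 0.158 | 1.317 | 1.186 | 1.05 |
| 10-45% | 0.0170 | 0.085 | 0.195 | 1.390 | 1.134 | 1.11 |

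The middle range implies a total ICC close to the planned 0.15; the widest exceeds it. Minimisation on household size balances time only approximately, so the actual excess should be a little smaller than the last column.

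**3. Simulation.** 278 households of three contacts, biased coin 0.7 within household-size groups, four periods, odds ratio 0.5, alpha 0.025, household-robust standard errors, no covariate other than period, 3,000 trials per setting. Power is on the risk-ratio scale:

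| Range | Without period | With period | Gain (points) | Excess of unadjusted SE over true SD, no effect |
|---|---|---|---|---|
| No drift | 92.5% | 92.5% | 0.0 | - |
| 20-35% | 90.4% | 91.2% | 0.8 | 1% |
| 15-40% | 89.0% | 91.0% | 2.0 | 4% |
| 10-45% | 84.8% | 89.6% | 4.8 | 9% |

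A separate simulation with three periods and mean rate 25% gave gains of 0.6, 2.0 and 4.7 points for 20-30%, 15-35% and 10-40%.

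**4. Scale.** In the three-period simulation the log risk ratio SE falls from 0.164 to 0.163, 0.167 to 0.161 and 0.169 to 0.156. The log odds ratio SE hardly moves: 0.201 to 0.201, 0.204 to 0.203 and 0.208 to 0.207. There the power gain comes from the estimate moving away from the null, for example from -0.645 to -0.692 in the widest range.

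**5. With vaccination in the model.** When individual vaccination, rising over time, was added to the data and to both models, the gains from period for the four-period ranges fell to 0.5, 1.3 and 2.9 points. Baseline antibodies and viral load were not modelled and could reduce them further.

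**The case against.** The strongest reply is that nothing in the article is wrong here. A long covariate list is pre-specified, allocation is concurrent, and the omission makes the test conservative at worst. That stands: this is a refinement of precision, not a correction of an error.

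Four stronger readings are tempting, and the documents do not support them:

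- *The comparison is biased by time.* It is not; the arms are randomised 1:1 over the same months.
- *Vaccine roll-out is ignored.* Both models adjust for vaccination status, and the transmission model adds contacts' antibody levels. Only variant and background transmission remain.
- *Every interval is visibly too wide and adjustment narrows it.* That is true of the risk ratio. On the odds-ratio scale the unadjusted SE also exceeds the true spread under drift, yet the adjusted interval has nearly the same width.
- *The test is clearly conservative even under mild drift.* At 20-35% the null rejection rate is 0.026 against a nominal 0.025. Marked conservatism (about 0.015) appears only at 10-45%.

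It is also fair that the widest range is a 4.5-fold change in attack rate, with a total ICC above the planned one, and that the article gives no rate by period and no local variant data. The missing control attack rate moves the power far more than this omission does.

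**Conclusion.** The point holds as a modest improvement to co-primary 2. Leaving out calendar period costs nothing if attack rates were stable, about 1 power point under mild drift, about 2 under moderate drift and 4-5 under extreme drift. These are upper bounds, because the simulated models contained none of the planned covariates. They rest on assumed period-specific rates, a mean control rate of 27.5% and a residual ICC of 0.12. A point or two is still worth having where the claimed 90% is only just reached. A reader might extend the loss to co-primary 1; no gain has been quantified there, and exact Fisher power on the plan's own inputs is already 93.9% at 139 per arm.

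**What to change.** Add calendar period of household randomisation to the co-primary 2 model and to its logit fallback. It can be four periods of equal household count cut by date, or a 3-df spline of randomisation date. Fix the form before unblinding and without sight of outcomes by arm. Adding the same term to co-primary 1 is optional.

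The date is available for every household, so no new data are needed. The cost is three more parameters in an already long model. With no drift the loss of power is nil, but the chance rises slightly that the log-link model fails to converge and the analysis moves to the odds ratio. The risk-ratio simulations used a log-link working model with robust errors and did not test that risk. The entry should also settle which link is primary, because the form of the gain depends on it.
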